### Relationship of AEs to the intervention

The relationship of AEs to study participation, particularly or medications will in most cases be clear. We use the following classification

. *definitely related* to study procedures such as surgery or anesthesia/analgesia (occurred during surgery or postoperatively),

. *probably related* to study procedures such as surgery or anesthesia/analgesia (occurred during surgery or postoperatively), but could arise from other causes,

. *possibly related* (occurred during participation, but could equally or more plausibly be ascribed to other causes), and

. *unrelated* (an event clearly explained by causes other than the trial participation ).

- The timing of AEs is divided into screening/enrollment/randomization, operative, postoperative and during longer-term follow up.

### Study Definition of Adverse Events

The anticipated adverse events are largely those associated with surgery or study medications. The description of anticipated potential AEs is given in Table 3. (This is in part based on the AE classification used for a NIH supported trial of male circumcision in Kisumu, Kenya). All medical officers are trained in the recognition and classification of the adverse events, and in the procedures required for reporting. The senior Medical Officers, is responsible for AE reports.

Any other serious events not defined in Table 3 are reported as SAEs.

**Table 3. Study Definition of Adverse Events**

| Adverse Event Type | Description of Adverse Event Type | Severity  and Codes |
| --- | --- | --- |

|  |  |  |
| --- | --- | --- |

| A. During Surgery |  |  |
| --- | --- | --- |

| Pain | Minor, not requiring additional anaesthesia | Mild (APS1) |
| --- | --- | --- |

|  | Moderate/severe controlled with additional anaesthesia* | Moderate (APS2) |
| --- | --- | --- |

|  | Severe, not controlled by additional anaesthesia | Severe (APS3) |
| --- | --- | --- |

| Excessive bleeding | More bleeding than usual, but easily controlled | Mild (ABL1) |
| --- | --- | --- |

|  | Bleeding that requires pressure dressing to control | Moderate (ABL2) |
| --- | --- | --- |

|  | Blood transfusion or transfer to another facility for management required | Severe (ABL3) |
| --- | --- | --- |

| Anesthetic-related event | Palpitations, vaso-vagal reaction or emesis | Mild (AAN1) |
| --- | --- | --- |

|  | Reaction to anesthetic requiring medical treatment in study clinic but not transfer to another facility | Moderate (AAN2) |
| --- | --- | --- |

|  | Anaphylaxis or any reaction requiring transfer to another facility | Severe (AAN3) |
| --- | --- | --- |

| Excessive skin removed | Adds time or material needs to the procedure, but does not result in any discernable adverse condition | Mild (AES1) |
| --- | --- | --- |
|  | Skin is tight, but additional operative work not necessary | Moderate (AES2) |

|  | Requires re-operation or transfer to another facility to correct the problem | Severe (AES3) |
| --- | --- | --- |

| Damage to the penis | Mild bruising or abrasion, not requiring treatment | Mild (ADP1) |
| --- | --- | --- |

|  | Bruise or abrasion to the glans or shaft of the penis requiring pressure dressing or additional surgery to control | Moderate (ADP2) |
| --- | --- | --- |

|  | Portion or all of the glans or shaft of the penis severed or burned by electrocautery | Severe (ADP3) |
| --- | --- | --- |

| B. First Month Post-Surgery |  |  |
| --- | --- | --- |

| Pain | Symptoms of pain requiring bed rest for less than half the day | Mild (BPA1) |
| --- | --- | --- |

|  | Pain requiring bed rest for more than half day | Moderate (BPA2) |
| --- | --- | --- |

|  | Excruciating pain requiring total bed rest | Severe |
| --- | --- | --- |

| Excessive bleeding | Dressing or other materials (for example underwear) spotted but dry | Mild (BBA1) |
| --- | --- | --- |

|  | Dressing or other materials wet with clotted blood requiring change of dressing | Moderate (BBA2) |
| --- | --- | --- |

|  | Dressing or other materials soaked with blood with obvious active bleeding requiring surgical exploration or transfusion | Severe (BBA3) |
| --- | --- | --- |

| Excessive skin removed | Client concerned but no discomfort on erection | Mild (BES1) |
| --- | --- | --- |

|  | Causes slight disconfort on erection but surgical correction not necessary. | Moderate (BES2) |
| --- | --- | --- |

|  | Interferes with life and surgical correction necessary | Severe (BES3) |
| --- | --- | --- |

| Insufficient skin removed | Prepuce partially covers the glans only when extended | Mild (BIS1) |
| --- | --- | --- |

|  | Prepuce still partially covers the glans and re-operation is required to correct | Moderate (BIS2) |
| --- | --- | --- |

|  | Not applicable |  |
| --- | --- | --- |

|  |  |  |
| --- | --- | --- |

| Swelling/Hematoma | More swelling than usual, but no treatment needed | Mild (BSH1) |
| --- | --- | --- |

|  | swelling requiring surgical exploration but no evidence of active bleeding | Moderate (BSH2) |
| --- | --- | --- |

|  | Rapidly expanding Heamatoma suggesting active bleeding requiring surgical exploration or referral | Severe (BSH3) |
| --- | --- | --- |

| Damage to the penis | Mild bruising or abrasion, not requiring treatment | Mild (BDP1) |
| --- | --- | --- |

|  | Bruise or abrasion to the glans or shaft of the penis requiring pressure dressing or additional surgery to control | Moderate (BDP2) |
| --- | --- | --- |

|  | Portion or all of the glans or shaft of the penis severed | Severe (BDP3) |
| --- | --- | --- |

| Infection | Pain and erythema with no obvious swelling | Mild (BIN1) |
| --- | --- | --- |

|  | Painful swelling with erythema or elevated temperature or purulent wound discharge | Moderate (BIN2) |
| --- | --- | --- |

|  | Cellulitis or wound necrosis | Severe (BIN3) |
| --- | --- | --- |

| Delayed wound healing | Healing takes longer than usual, but no extra treatment necessary | Mild (BDW1) |
| --- | --- | --- |

|  | Additional non-operative treatment required | Moderate (BDW2) |
| --- | --- | --- |

|  | Requires re-operation to correct | Severe (BDW3) |
| --- | --- | --- |

| Appearance | Client concerned, but no discernable deformity | Mild (BAP1) |
| --- | --- | --- |

|  | Minimal deformity does not require re-operation | Moderate (BAP2) |
| --- | --- | --- |

|  | Significant deformity requires re-operation to correct | Severe (BAP3) |
| --- | --- | --- |

| Problems with voiding | Transient complaint that resolves without treatment | Mild (BVO1) |
| --- | --- | --- |

|  | Requires a special return to the clinic, but no additional treatment required | Moderate (BVO2) |
| --- | --- | --- |

|  | Requires referral to another facility for management | Severe (BVO3) |
| --- | --- | --- |

| Wound dehiscence | Wound disruption involving no more than one principal suture. | Mild (BWD1) |
| --- | --- | --- |
|  | Wound disruption and involving two or more principal sutures. No surgical intervention required. | Modarete (BWD2) |
|  | Significant wound disruption requiring surgical correction | Severe (BWD3) |
|  |  |  |

| **C. One Month or More Post-Surgery** |  |  |
| --- | --- | --- |

| Infection** | Pain and erythema no obvious swelling | Mild (CIN1) |
| --- | --- | --- |

|  | Painful swelling/purulent wound discharge | Moderate (CIN2) |
| --- | --- | --- |

|  | Cellulitis or wound necrosis | Severe (CIN3) |
| --- | --- | --- |

| Delayed wound healing | Healing takes longer than usual, but no extra treatment necessary | Mild (CDW1) |
| --- | --- | --- |

|  | Additional non-operative treatment required | Moderate (CDW2) |
| --- | --- | --- |

|  | Requires re-operation to correct | Severe(CDW3) |
| --- | --- | --- |

| Appearance | Client concerned, but no discernable deformity | Mild (CAP1) |
| --- | --- | --- |

|  | Significant scarring or other cosmetic problem, but does not require re-operation | Moderate (CAP2) |
| --- | --- | --- |

|  | Requires re-operation to correct | Severe (CAP3) |
| --- | --- | --- |

| Excessive skin removed | Client concerned, but there is nodeformity on erection | Mild (CES1) |
| --- | --- | --- |

|  | Causes slight discomfort on erection but surgical correction not necessary | Moderate (CES2) |
| --- | --- | --- |

|  | Interferes with sexual life and surgical correction is necessary | Severe (CES3) |
| --- | --- | --- |

| Insufficient skin removed | Prepuce partially covers the glans only when extended | Mild (CIS1) |
| --- | --- | --- |

|  | Prepuce still partially covers the glans and re-operation is required to correct | Moderate (CIS2) |
| --- | --- | --- |

|  | Not applicable |  |
| --- | --- | --- |

|  |  |  |
| --- | --- | --- |

|  |  |  |
| --- | --- | --- |

| Torsion of penis | Torsion is observable, but does not cause pain or discomfort. | Mild (CTP1) |
| --- | --- | --- |

|  | Causes mild pain or discomfort on erection, but additional operative work not necessary | Moderate (CTP2) |
| --- | --- | --- |

|  | Requires re-operation or transfer to another facility to correct the problem | Severe (CTP3) |
| --- | --- | --- |

|  |  |  |
| --- | --- | --- |

| Erectile dysfunction | Client reports occasional inability to have an erection | Mild (CED1) |
| --- | --- | --- |

|  | Client reports frequent inability to have an erection | Moderate (CED2) |
| --- | --- | --- |

|  | Client reports complete or near complete inability to have erections | Severe (CED3) |
| --- | --- | --- |

| Psycho-behavioral problems | Client reports mild sexual dissatisfaction attributed to circumcision, but no significant psycho-behavioural consequences | Mild (CPB1) |
| --- | --- | --- |

|  | Client reports significant sexual dissatisfaction attributed to circumcision, but no significant psycho-behavioural consequences | Moderate (CPB2) |
| --- | --- | --- |

|  | Significant depression or other psychological problems attributed by the participant to the circumcision | Severe (CPB3) |
| --- | --- | --- |

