### Post-operative Evaluations

The schedule of postoperative evaluations for stage 2 of the trial is given in Figures 2

1st post operative visit <48 hrs of surgery.

2nd post operative visit at 7 ± 2 days following surgery.

3rd post operative visit 3-6 weeks following surgery

Unscheduled visits can occur at any time if a participant experiences problems. Participants can contact the project via community counselors who are equipped with cell phones. If wound healing is incomplete at visit 3, men will be followed weekly until wound healing is certified.

These visits, which can take place in the participant’s home or at a convenient central location (“hub”), will record AEs, symptoms, resumption of intercourse, assessment of condom use, examination of the wound and collection of a culture swab if there is evidence of infection, evaluation of wound healing and certification if healing is complete.

Under this amendment, all HIV+ subjects and a sub sample of about 200 HIV negative men enrolled in the Gates funded trial will be followed at weekly intervals until complete wound healing is documented. At each visit, including the currently scheduled one and four week visits, the wound will be inspected using a magnifying glass, and records maintained of the development of scar tissue, scabs, breaches in skin integrity, adsorption of sutures, stitch sinuses, wound dehiscence, infection, hematoma and bleeding. The anatomic site of any problems will be noted. Follow up will continue until all AEs have been resolved. Records will also be maintained of wound care, resumption of intercourse and condom use. A SOP will be developed to ensure uniform certification of wound healing by clinical officers. Digital photographs may be taken to document lesions with the participant’s permission and will not include identifying facial features.. The participant will be asked to sign the photograph indicating their permission.

Consideration will be given to use of Imalux Optical Coherence Tomography (OCT) to monitor scar formation and depth (1-2 mm). However, the cost of this equipment is $60,000 and there would be delays in purchase, shipping and training for use. Therefore, rather than delay circumcision in HIV+ men, we propose to monitor healing visually until decisions on purchase of OCT equipment have been made.

At each weekly postoperative visit 5 mL of venous blood will be collected for determination of HIV viral load to assess whether surgery affects men’s viremia.

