We firmly believe that exclusion of HIV positive men from these trials would create major ethical dilemmas and preclude the investigation of important safety issues critical to future programmatic and clinical practice. Thus, we believe that these trials can only be ethically conducted in a community setting if both HIV-negative and HIV-positive men are enrolled*.* We anticipate that the DSMB would carefully scrutinize data on circumcision of HIV positive men, and if the DSMB found evidence of risk to either to HIV positive men or their partners, the study would modified according to DSMB recommendations **The findings at the December 19, 2006 and March 1, 2007 reviews suggested non-significant higher rates of male-tofemale HIV transmission in the intervention arm, largely among couples who resumed sex prior to wound healing. The moderate and severe surgical complications among HIV+ men (3.2%) were comparable to those in HIV-negative men (3.6%), although wound healing may have been somewhat slower in the HIV+ men. Circumcision reduced the rates of GUD in HIV+ men.**

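### Table 3 has no late codes for several wound events, some of which staff must still record, so the same event can be graded differently before and after one month

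*Protocol*

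**What the plan says.** Table 3 (section 7.4.4) defines adverse events by time since surgery. Part B covers the first month; the next part is headed "C. One Month or More Post-Surgery".

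Section 6.3.1 sets the wound follow-up. The schedule has a "3rd post operative visit 3-6 weeks following surgery", and then: "If wound healing is incomplete at visit 3, men will be followed weekly until wound healing is certified". Under the amendment in the same section, all HIV+ men and about 200 HIV-negative men are seen weekly until healing. The findings to be recorded at each visit include "stitch sinuses, wound dehiscence, infection, hematoma and bleeding". No one-month limit is attached.

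Moderate infection in part B reads "Painful swelling with erythema or elevated temperature or purulent wound discharge"; in part C it reads "Painful swelling/purulent wound discharge".

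For events outside the table, section 7.4.4 says: "Any other serious events not defined in Table 3 are reported as SAEs".

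Safety in HIV+ men and their partners is primary objective 2. Section 10.7.3 summarizes surgical safety by moderate and severe complications, 3.2% in HIV+ men against 3.6% in HIV-negative men, and adds "although wound healing may have been somewhat slower in the HIV+ men".

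**The concern.** Staff are told to look for, and write down, wound events in a period for which the definition table has no matching codes. A medical officer who finds a mild or moderate dehiscence at week 5 must either force it into another row, such as delayed wound healing, or grade it on the general severity scale. Neither route is bound to give the grade that the same finding would have had a week or two earlier.

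This matters because the safety summary counts moderate and severe events together. The line between mild and moderate decides what enters that count, and it should not move at a fixed date while wounds are still open. Late disruption of an unhealed wound is also of particular interest here: the weekly follow-up was introduced because interim data suggested more male-to-female transmission in couples who resumed sex before certified healing.

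**Working it through.** **1. Rows compared.** Part B lists 11 event types and part C lists 8. Five types appear in both: infection, delayed wound healing, appearance, excessive skin removed and insufficient skin removed. Six part B types have no part C row: dehiscence, excessive bleeding, swelling/hematoma, pain, voiding problems and damage to the penis. Three are new in part C: torsion, erectile dysfunction and psycho-behavioral problems.

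**2. Overlap in time.** Visit 3 falls on days 21 to 42. Taking a month as 28 to 30 days, the part of that window in part C is (42 − 30)/21 = 0.57 to (42 − 28)/21 = 0.67. This is a share of calendar days, not of events. It shows only that the two schedules overlap. All weekly visits after week 6 also fall in part C.

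**3. What the other rules cover.**
- Section 7.4.1 defines an adverse event broadly and without a time limit, so a late dehiscence is still an adverse event. The same section then points to Table 3 for the definitions.
- The catch-all in section 7.4.4 takes serious events only.
- Section 7.4.2 gives a general scale: mild if transient with activity unaffected, moderate if activity is modified or extra intervention is needed.
- The added codes (under New AE codes, after Table 3) include a joint dehiscence and infection code built from part B codes, and a part C code for stitch granuloma. They include no late dehiscence, bleeding or hematoma code.

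**4. The same event on either side of one month.** Late dehiscence is placed in the nearest surviving row, delayed wound healing.

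| Event | First month | One month or more | Shift |
|---|---|---|---|
| Disruption at two or more principal sutures, no extra treatment, activity unaffected | Moderate (BWD2) | Mild (CDW1, or section 7.4.2 if transient) | Down |
| Disruption at one principal suture, extra non-operative treatment | Mild (BWD1) | Moderate (CDW2) | Up |
| Disruption needing surgical correction | Severe (BWD3) | Severe (CDW3) | None |
| Voiding problem needing a special return, no treatment, activity unaffected | Moderate (BVO2) | No row; mild on section 7.4.2 if transient | Down |

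**5. Infection.** Mild and severe are essentially unchanged; only moderate differs. Suppose BIN2 means painful swelling together with any one of erythema, raised temperature or purulent discharge, and CIN2 means painful swelling or purulent discharge. Then CIN2 is wider and late infections are graded up. If raised temperature alone satisfies BIN2, such a case is moderate before one month and not after. The footnote to part C infection lists raised temperature as a sign of infection but assigns it no grade.

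**6. Sensitivity of the rate.** The number of circumcised HIV+ men behind the 3.2% is not stated. Assume 400 to 500: the summary table plans about 800 HIV+ men in all, so 400 per arm, and section 8.4 uses 500 per arm. Then 3.2% is 0.032 × 400 = 12.8 to 0.032 × 500 = 16 events. One regraded man moves the rate by 1/500 = 0.20 to 1/400 = 0.25 percentage points, in either direction. The 0.4-point difference from HIV-negative men corresponds to 0.004 × 400 = 1.6 to 0.004 × 500 = 2 men. This shows how few regradings would register. It does not estimate how many occurred.

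**The case against.** The strongest reply is that nothing is lost. Section 7.4.4 presents Table 3 as describing anticipated events, not as a closed list. The general definition has no time limit, the general scale can grade any event, delayed healing keeps three grades in part C, and section 6.3.1 has wound findings recorded and adverse events followed to resolution. This stands as far as capture goes: a late dehiscence is recorded and can be graded. It does not answer the grading point, because BWD2 is moderate on anatomy alone, whereas the general scale and CDW1 turn on treatment or activity.

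A reader might go further and infer that late wound harm in HIV+ men is undercounted or downgraded, so that they look safer than they are. The protocol does not support that:

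- Grade shifts run both ways, and the infection change depends on how BIN2 is read.
- Slower healing in HIV+ men is stated only as a possibility, and Table 3 applies to every circumcised man.
- Weekly inspection covers all HIV+ men but only about 200 HIV-negative men, which favors finding more late events in HIV+ men. That schedule followed the March 2007 review, so it bears on later data and not on the rates reported from the reviews up to that date.
- The protocol gives no count of late events and does not say which time windows the 3.2% and 3.6% cover.
- No section says events are placed in part B or C by visit date. The section on tabulation of AEs uses time since surgery and event dates.

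**Conclusion.** The inconsistency between Table 3 and section 6.3.1 is real and should be corrected. Mild and moderate dehiscence, bleeding and hematoma must be recorded until healing is certified, but have no Table 3 code after one month. Late pain and voiding problems also have no row, and moderate infection has two wordings. The consequence is limited to coding and grading: the moderate/severe rate for primary objective 2 may rest on two different grading rules. The size and net direction are unknown, and so is whether HIV+ men are affected more than HIV-negative men. The sensitivity in step 6 rests on an assumed 400 to 500 circumcised HIV+ men. The dehiscence shifts assume that late events are coded as delayed healing or graded on the general scale. The protocol gives no ground for saying that the reported comparability of HIV+ and HIV-negative men is wrong.

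**What to change.** Reconcile Table 3 with section 6.3.1:

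- Let the part B wound-event codes and grades apply until healing is certified, or add part C rows for dehiscence, bleeding, swelling/hematoma, pain and voiding problems with the same grading.
- Use one definition of moderate infection in both parts, worded so that it is clear which signs are required together and which are alternatives.
- Tabulate moderate and severe events by HIV status on that single grading, stating the time window covered.
- Regrade late wound events already on the adverse event, unscheduled-visit and post-operative forms.

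No new visits or data are needed. The cost is a table revision and a small recoding task, and the stated rates may change slightly in either direction.

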**COMMENTS:**

* Additional anesthesia implies a volume of local anesthetic in excess of initial amount drawn up in the syringe and calculated to be sufficient for patient’s weight before surgery.

** Infection is indicated by swelling, erythema, pain, elevated temperature (locally or systemically, or purulent discharge)

**New AE codes**

During the February 2006 review, it was decided that specificity could be improved by addition of new codes. This did not affect the diagnosis of AEs, but added more detail for future analyses. The additional codes were:

1. A new code for joint dehiscence (BWD) and infection (BIN) AEs, indicated by BWD/BIN. Degree of severity is per individual event and the first event to occur is reported first.

2. New codes for stich sinus: SS = Sinus at Suture site SS1 = Sinus with non-puss discharge SS2 = Sinus with purulent discharge. This would be included in infectious AEs, but adds specificity.

3. New code for anatomical site of lesion (F = Frenulum), because many wound dehiscence, poor skin apposition and infection involved the frenulum.

4. New codes for pain on intercourse: PI = Pain on Intercourse PI1 = No interference with sex, PI2 = Reduced sexual frequency, PI3 = Refrain from intercourse due to pain

5. A new code was added for allergic reaction to the iodine prep, since we observed cases of blisters following surgical site preparation

PREP REACTION APR 1 = MILD BLISTERS RESOLVED

APR 2 = MORE SEVERE BLISTERS REQUIRING TREATMENT

6. A number of cases of pain or wound dehiscence occurred after intercourse, so we coded intercourse related AEs: I = RELATIONSHIP TO INTERCOURSE

7. A number of cases of wound dehiscence were due to external trauma (e.g., heavy lifting, bicycle accidents) so this was coded as EX = EXTERNAL CAUSE

8. Code for stitch granuloma: SG=Stitch granuloma. CSG 1=Small capable of resolving,no need for surgical removal. CSG 2=Not capable of resolving, requires surgical intervention. CSG 3=Not applicable

No changes were made to the AE definitions, although with hindsight, we believe these could be improved for monitoring of control surgery related AEs.

